## Schedule of events

Table 3. Schedule of investigational events.

|  | Preop Visit | Day of treat-ment | 1  In-hospital | 2  In-hospital | 3  Out-patient | 4  Out-patient | 5  Out- patient | 6  Out-patient | 7  EOS |
| --- | --- | --- | --- | --- | --- | --- | --- | --- | --- |
|  | -1m | 0 d | 5 d ± 2 | 10 d ± 3 | 30 d +2m | 90 d  ±4m | 1y ±3m | 3 y ±3m | 5 y ±3m |
| Physical examination  (eCRF follow-up) | x |  | x | x |  |  |  |  |  |
| Telephone follow-up  (eCRF follow-up) |  |  |  |  | x | x | x | x |  |
| eCRF Inclusion/screening | x |  |  |  |  |  |  |  |  |
| Signed informed consent | x |  |  |  |  |  |  |  |  |
| Randomization* |  | x* |  |  |  |  |  |  |  |
| CRS + HIPEC/EPIC treatment data  HIPEC registry treatment section |  |  |  |  |  | x |  |  |  |
| eCRF Drugs – medication/chemotherapy** | x |  |  |  |  | x |  |  |  |
| CT scan |  |  |  |  |  |  | x |  |  |
| eCRF Blood work*** |  |  |  |  | x |  |  |  |  |
| Questionnaire (QLQ-C30, CR29, STO22) HIPEC registry acquired | x |  |  |  |  | x | x | x |  |
| Morbidity from HIPEC registry (incl. eCRF AER/eCRF follow-up) |  |  | x | x | x |  |  |  |  |
| Overall survival HIPEC registry§ |  |  |  |  |  |  |  |  | x |
| Recurrence free survival HIPEC registry |  |  |  |  |  |  | x | x | x |

* only after the maximum tolerated dose of 5-FU has been determined

** (-1m) – previous chemotherapy and current medications, (90d) adjuvant chemotherapy administered

*** CEA, CA 19-9, CA 125 are taken preoperatively (-1m). Haemoglobin, C-reactive protein (CRP), white blood cell count (WBC), neutrophil count, platelet count, albumin, creatinine, alanine transaminase (ALT) are taken preoperatively and postoperatively 5 times during the first 10 days. The lowest haemoglobin, highest CRP, lowest neutrophil and WBC, lowest platelet count, lowest albumin, highest creatinine, highest ALT will be registered in the eCRF blood work.

§ Overall survival from HIPEC registry is also acquired prior to interim analysis

## END OF STUDY

The end of study (EOS) is defined as 5 years after the last patient was included in the study, when long-secondary outcomes can be evaluated.

# SELECTION AND WITHDRAWAL OF SUBJECTS

## Subject inclusion criteria

1. Provision of written informed consent prior to any study specific procedures
2. ECOG Performance Status Score 0,1 or 2 alternatively Karnofsky 60-100
3. Adequate kidney, liver, bone marrow function according to laboratory tests
4. For females of childbearing potential, a negative pregnancy test must be documented
5. ≥ 18 years old and <75 years old.
6. Colorectal cancer with peritoneal metastases with or without liver metastases. The liver metastases have to have been removed prior to CRS+HIPEC or at the same time as the CRS+HIPEC. Maximum 3 simple liver metastases requiring non-complex liver resections.
7. All patients deemed eligible for CRS and HIPEC according to clinical routine

## Subject exclusion criteria

1. Previous severe toxicity/allergic reactions to systemic chemotherapy agents oxaliplatin or irinotecan or 5-FU
2. Unable to tolerate intensified HIPEC treatment due to comorbidity
3. Metastasis other than peritoneum or liver
4. Complex liver-perenchymal sparing surgery or hemihepatectomy procedures are to be excluded.
5. Previous CRS or HIPEC
6. Pregnant or lactating (nursing) women
7. Active infections requiring antibiotics
8. Active liver disease with positive serology for active hepatitis B, C, or known HIV
9. Concurrent administration of any cancer therapy other than planned study treatment within 4 weeks prior to and up to 4 weeks after study treatment
10. Incomplete cytoreduction defined as completeness of cytoreduction score 1-3
11. Histopathology of other origin than colorectal cancer

## Withdrawal of subjects

The time from randomization to administration of intraoperative chemotherapy treatment is very short, basically a few hours. Thus, subject withdrawal will in principle not occur after randomization and prior to treatment. However, withdrawal may occur due to intraoperative complications leading to no HIPEC treatment administration. As these patients will not be randomized, they will not be included in the trial other than as a part of the fallout between informed consent and randomization.

Naturally, patients may opt to withdraw for any reason from the trial. In that case, all data collected up to the point of withdrawal will be included in the trial. No further quality of life questionnaires will be sent out after withdrawal has been requested. All other follow-up will also be discontinued.

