## RandomiZation and blinding

Patient randomization will be integrated into the HIPEC registry and will be performed intraoperatively after abdominal exploration and after a CC 0 result is deemed achievable. For patients with isolated peritoneal metastases, there will be center stratification and PCI stratification (PCI 1-10 vs 11+). For patients with combined liver and peritoneal metastases, there will be only PCI stratification (PCI 1-10 vs 11+). Multivariable regression will be used in the results section in order to account for skewed differences in baseline differences. See the planned statistical analyses (13.2).

There is no blinding involved in this trial. This is mainly due to the fact that one arm will need to receive G-CSF treatment postoperatively; and thus, the treating physician needs to know which arm the patient is allocated to. The primary endpoint is recurrence free survival which is determined by radiologists on a CT scan. The radiologists will not be privy to the treatment allocation. Thus, there is a blinding of primary endpoint evaluation.

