## Intention-to-treat analysis

The trial will be intention-to-treat. Thus, all patients being randomized are included in the trial. Since treatment is administered within hours of randomization, there will likely be no or minimal fallout of subjects between randomization and treatment administration.

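### Section 9.3 treats patients who receive no HIPEC as never randomized, which conflicts with randomizing before HIPEC (10.5) and with keeping all randomized patients (13.7)

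*Protocol*

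**What the plan says.** Four places in the Protocol bear on this.

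- **Section 9.3, Withdrawal of subjects.** It opens with the order of events: "The time from randomization to administration of intraoperative chemotherapy treatment is very short, basically a few hours". It infers that withdrawal between randomization and treatment should in principle not happen, and then gives an exception: "However, withdrawal may occur due to intraoperative complications leading to no HIPEC treatment administration". On these patients it concludes: "As these patients will not be randomized, they will not be included in the trial", except as losses between consent and randomization.
- **Section 10.5, Randomization and blinding.** Randomization is "performed intraoperatively after abdominal exploration and after a CC 0 result is deemed achievable". The section also states that the trial is unblinded; only the radiologists reading the CT scans are kept unaware of allocation.
- **Section 13.7, Intention-to-treat analysis.** Under intention-to-treat, "all patients being randomized are included in the trial". It expects little or no loss between randomization and treatment, but does not rule it out.
- **Section 9.2, Subject exclusion criteria.** Exclusion 10 is "Incomplete cytoreduction defined as completeness of cytoreduction score 1-3". Exclusion 9 bars other cancer therapy "within 4 weeks prior to and up to 4 weeks after study treatment".

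**The concern.** A patient whose complication arises after randomization but before HIPEC is a randomized patient. Section 9.3 describes such a patient as not randomized and outside the trial; section 13.7 puts the same patient inside it. Sites recording participant flow and analysts building the analysis set have no single rule.

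The surgical team knows the allocation, and arm B is the more intensive regimen. After a complication, whether HIPEC goes ahead could depend on the arm. If untreated patients were then recorded as never randomized, the arms could be selected differently, and the participant flow would not show it. Blinded CT reading does not protect against this, because the problem lies in who is counted, not in how recurrence is read.

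**Working it through.** **1. Order of events**

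| Step | Source | Status of the patient |
| --- | --- | --- |
| Consent at the preoperative visit | 8.3, 13.1 | Not randomized |
| Exploration; CC 0 judged achievable | 10.5 | Not randomized |
| Randomization | 10.5 | Randomized |
| Remaining surgery, up to a few hours | 9.3, 9.4 | Randomized |
| HIPEC given or not given | 9.3, 10.7 | Randomized |

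A complication in the first two steps fits the wording of 9.3. One in the fourth step does not, yet that is the interval 9.3 has just been discussing when it introduces its exception. Section 10.7 also provides for drug that is ordered and then not given because of an unforeseen event during surgery, so the protocol foresees non-administration.

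**2. Exclusion criteria**

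- Exclusion 10 depends on the final CC score. Randomization rests on a forecast of it, so a score of 1-3 can emerge after randomization.
- Exclusion 9 has two halves. The 4 weeks before treatment can be checked in advance; the 4 weeks after cannot.
- No section says how a randomized patient who later meets either criterion is handled. Section 13.3 adds 10% for loss to follow-up or violations, which leaves open whether violators leave the analysis.

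**3. The plan's sample size**

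Inputs from 13.3: 12-month RFS 50% and 66%, alpha 5% (taken as two-sided), and the stated beta of 80% read as power. With mean rate 0.58:

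n = [1.960 × √(2 × 0.58 × 0.42) + 0.842 × √(0.50 × 0.50 + 0.66 × 0.34)]² / 0.16² ≈ 148.2, which rounds up to 149 per arm against 148 stated. Then 148 × 1.10 = 162.8, so 163 per arm and 326 in total. The plan's figures reproduce and do not depend on the disputed sentence.

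**4. Possible shift in one arm**

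Let w be the share of one arm removed and r the 12-month RFS among those removed. Both are assumptions, since the documents give neither. For an arm with true RFS of 50%:

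shift = (0.50 − w × r) / (1 − w) − 0.50 = w × (0.50 − r) / (1 − w)

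| w | r = 30% | r = 20% |
| --- | --- | --- |
| 2% (about 3 of 163) | 0.02 × 0.20 / 0.98 = 0.4 points | 0.02 × 0.30 / 0.98 = 0.6 points |
| 5% (about 8 of 163) | 0.05 × 0.20 / 0.95 = 1.1 points | 0.05 × 0.30 / 0.95 = 1.6 points |

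Over a wider range (w from 1% to 5%, r from 0% to 30%) the shift runs from 0.2 to 2.6 points. If equal shares with the same r left both arms and there were no true effect, the shifts would cancel.

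**5. Power**

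Power is 83.6% at 163 per arm. Removing 1%, 3% or 5% of both arms (about 3, 10 or 16 of 326) gives 83.3%, 82.5% or 81.7% before any other loss. Power is a minor matter here.

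**The case against.** The strongest defence is that the sentence in 9.3 concerns only patients not yet randomized. It continues past the words quoted above: "As these patients will not be randomized, they will not be included in the trial other than as a part of the fallout" between consent and randomization. Patients consent before surgery and are randomized only after exploration, so complications before randomization are a real category, and leaving those patients out is correct. Section 13.7, which governs the analysis, already states the right principle. This has force: the authors may well have meant only that group. But the text does not say so, and the exception is attached to the interval after randomization. The sentence needs correcting either way.

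A reader might infer that the protocol plans to delete randomized patients, or that exclusions 9 and 10 remove anyone found in breach after randomization. The documents do not support that. No text says a breach found later takes a patient out of the analysis, and 13.7 points the other way. For these criteria there is a timing gap with no stated handling, not a rule of removal.

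It is also fair to say that bias is not shown. Nothing in the protocol says the decision to give HIPEC depends on the arm, section 10.1 allows a 25% dose reduction in both arms, and the illustration takes patients from one arm only at rates the documents do not give. Finally, the main efficacy part of section 13.2.1 refers to an updated analysis plan in an appendix that is not shown, so whether the analysis set is clarified there cannot be checked. That does not repair 9.3, which is the text the sites work from.

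**Conclusion.** The contradiction is real: 9.3 conflicts with its own opening sentence, with 10.5 and with 13.7. As worded, it could lead to randomized, untreated patients being left out of an intention-to-treat trial, possibly unequally between arms.

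The size is unknown and probably small. A shift of 0.4-1.6 points is at most a tenth of the planned 16 (1.6 / 16), and it rests on assumed removal of 2-5% from one arm only with an assumed RFS of 20-30% among those removed. The protocol itself expects little or no such loss. It would be wrong to conclude that the primary comparison is biased; the supported statement is that it could be. Such a bias would, however, be systematic, so recruiting more patients would not remove it. The sample size stands.

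The point about eligibility is limited to exclusion 10 and the second half of exclusion 9. It is one of timing and unstated handling.

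**What to change.** - **Section 9.3.** Say that only patients whose complication occurs before randomization count as losses between consent and randomization. Say that every randomized patient stays in the allocated arm and is followed up, whether or not HIPEC is given.
- **Section 9.2.** Say that a final CC score of 1-3, or other cancer therapy given within the period after study treatment, if found after randomization, is a protocol deviation and the patient stays in the intention-to-treat set, consistent with 13.7.

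This changes wording only. It adds no patients and says nothing about when HIPEC should be given. The cost is slight dilution. If 2% or 5% of arm B were untreated and had the control rate of 50%, the planned 16 points would become 16 × 0.98 = 15.7 or 16 × 0.95 = 15.2. The intention-to-treat analysis already chosen accepts that cost.

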## Accountability of investigational products

The study requires a less rigorous accountability as the use of both drugs is commonplace in routine oncological treatment of colorectal cancer. The drug is ordered from the operating room the same morning that it is administered. It is delivered approximately 1-2 hours after a prescription is sent to the pharmacy from the operating room. If the products are not administered as planned due to an unforeseen event during surgery, they will be returned to the pharmacy for destruction and logged as not administered. This will be noted in the registry treatment follow-up.

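### Section 9.3 treats every patient whose HIPEC is abandoned for intraoperative complications as never randomised, which is false in the hours between randomisation and HIPEC and conflicts there with the intention-to-treat rule in 13.7

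*Protocol*

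**What the plan says.** **Timing.** Section 10.5 (Randomization and blinding) states that randomisation "will be performed intraoperatively after abdominal exploration and after a CC 0 result is deemed achievable". Section 9.3 (Withdrawal of subjects) adds: "The time from randomization to administration of intraoperative chemotherapy treatment is very short, basically a few hours". Section 9.4 also places treatment within hours of randomisation.

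**Abandoned HIPEC.** Section 9.3 first says that withdrawal between randomisation and treatment should in principle not happen. It continues: "However, withdrawal may occur due to intraoperative complications leading to no HIPEC treatment administration". The next sentence gives the handling: "As these patients will not be randomized, they will not be included in the trial other than as a part of the fallout" between consent and randomisation.

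**Analysis population.** Section 13.7 declares an intention-to-treat trial: "Thus, all patients being randomized are included in the trial". It adds that "there will likely be no or minimal fallout of subjects between randomization and treatment administration".

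**Related text.** Section 10.7 foresees treatment that is ordered but not given: "If the products are not administered as planned due to an unforeseen event during surgery, they will be returned to the pharmacy", and the event is noted in the registry. On masking, section 10.5 says: "There is no blinding involved in this trial". Only the radiologists who read the CT scans are kept unaware of the arm.

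**The concern.** Section 9.3 states as a fact that a patient who gets no HIPEC because of an intraoperative complication has not been randomised. By the protocol's own order of events that is true only if the complication comes before randomisation. In the hours that follow, the patient already has an allocation, and the two sections put the same patient in different places: 9.3 in the pre-randomisation fallout, 13.7 in the analysis set.

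What is at stake is the protection that randomisation gives. Abandoning HIPEC is a decision taken after allocation in an open-label trial. If patients leave the comparison on the strength of that decision, the arms that remain are no longer purely the product of randomisation. This would affect 12-month RFS, overall survival and the 30-day complication rates. Masked CT reading does not help, because the selection comes before the scan.

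The problem also cannot be left to the analysis stage alone. Section 9.3 tells sites whom to keep in the trial. A patient logged as fallout has no trial requirement for the 12-month CT entry. Routine Swedish follow-up and the registry may still hold part of that information.

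**Working it through.** **1. Order of events**

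| Step | Source | Status of a patient whose HIPEC is abandoned at this step |
|---|---|---|
| Consent at the preoperative visit | 13.1 | Not randomised: 9.3 is right |
| Exploration, up to the judgement that CC 0 is achievable | 10.5 | Not randomised: 9.3 is right |
| Randomisation in the registry | 10.5 | – |
| A few hours until intraoperative chemotherapy | 9.3, 9.4 | Randomised: 9.3 is wrong, 13.7 applies |
| HIPEC (arm A) or HIPEC followed by EPIC (arm B) | 10.1 | – |

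The reason given in 9.3 fails in the fourth row. Section 13.7 accepts that this row may contain patients, since it expects few losses there rather than ruling them out.

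**2. Knowledge of the arm.** Section 10.5 says there is no blinding and that the treating physician must know the allocation. Section 10.7 has the drugs ordered from the operating room, and the regimens differ by arm (10.1). That the operating surgeon knows the arm is an inference from these statements; the protocol does not say so of the surgeon by name.

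**3. The plan's own figure.** Section 13.3 gives 148 per arm for 50% versus 66% RFS at 12 months, with 5% alpha and 80% power. Taking alpha as two-sided, the pooled normal formula gives 149 and the arcsine formula 147.95, so the figure reproduces. The 10% allowance gives 148 × 1.10 = 162.8, i.e. 163. No stated number is in dispute.

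**4. Possible size of the bias.** The abandonment rates and the prognosis of these patients are assumptions, because the protocol gives neither. Assume no true effect, with 50% RFS among all randomised patients in each arm. Let *f* be the fraction dropped and *r* their RFS. The RFS of those who remain is

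(0.50 − *f* × *r*) / (1 − *f*)

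With *f* = 0.02 in one arm and 0.05 in the other:

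| *r* | *f* = 0.02 | *f* = 0.05 | Spurious difference |
|---|---|---|---|
| 0.10 | 0.498/0.98 = 50.82% | 0.495/0.95 = 52.11% | 1.29 points |
| 0.20 | 0.496/0.98 = 50.61% | 0.490/0.95 = 51.58% | 0.97 points |
| 0.30 | 0.494/0.98 = 50.41% | 0.485/0.95 = 51.05% | 0.64 points |

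With 163 per arm, these fractions are about 3 and 8 patients (163 × 0.02 = 3.3; 163 × 0.05 = 8.2). The spurious benefit goes to whichever arm loses more. If both arms have the same *f* and the same *r*, the two expressions are equal and the difference under the null is zero.

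**5. Effect on the false-positive rate.** The calculation uses a normal approximation, 163 randomised per arm and dropped patients at 0–25% RFS. Dropping 2% and 5% gives a two-sided type I error of 5.2–5.9% instead of 5%. Dropping 5% from one arm only gives 5.6–7.5%.

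**The case against.** The best defence is that 9.3, read literally, excludes nobody who has been randomised. It speaks of patients who will not be randomised and assigns them to an interval that ends at randomisation. Such patients exist, because consent comes at the preoperative visit and a complication before the CC 0 judgement can end the plan for HIPEC. On this reading 9.3 and 13.7 cover different patients. The note in 10.7 that undelivered drug is recorded in the registry also fits keeping the patient under follow-up.

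This reading is possible, and it is what the rule should say, but the text does not say it. The sentence on intraoperative complications opens as an exception to the preceding one, which is about the period after randomisation and before treatment. It sets no limit on when the complication occurs. A site could reasonably record a randomised patient as fallout.

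Other parts of the defence stand. Section 13.7 is an explicit intention-to-treat rule and expects few or no cases. Section 10.1 allows a dose reduction in either arm, so worry about intensity need not end in abandonment.

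A reader might infer that most complications leading to no HIPEC arise after randomisation, or that surgeons would abandon HIPEC more readily before the intensified regimen, so that the bias favours arm B. The documents support neither. They do not say when such complications occur, and they give no abandonment rate for either arm.

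**Conclusion.** The defect is real and is one of wording. For complications between randomisation and HIPEC, 9.3 rests on a false premise and contradicts 13.7, and nothing says which section governs. It would be too strong to say that the plan removes randomised patients: that happens only if a site applies 9.3 in this window in preference to 13.7.

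The likely effect is small. Under the assumed 2% versus 5% abandonment and 10–30% RFS in those patients, it is about 0.6–1.3 points of 12-month RFS, or 4–8% of the 16-point design effect (0.64/16 and 1.29/16). Its direction is uncertain, and it is nil under the null if abandonment and prognosis are equal in both arms. These sizes rest wholly on assumed rates. The contradiction does not, and since it touches the population for the primary comparison it should be removed.

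**What to change.** Change section 9.3 in three respects:

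- Limit the fallout sentence to patients in whom HIPEC is abandoned before randomisation has been executed in the registry.
- State that any randomised patient who then does not receive HIPEC or EPIC, for whatever reason, stays in the assigned arm, is followed as planned including the 12-month CT, and is analysed by intention to treat as in 13.7.
- Record the reason for each case in the registry and report the counts by arm, so that any imbalance can be seen.

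The cost is a wording change and one recorded item. The target stays at 163 per arm, 326 in total. Keeping a few untreated patients slightly dilutes the estimated effect. For example, if 5% of each arm were untreated with the same RFS in both arms, a 16-point difference among treated patients would appear as 0.95 × 16 = 15.2 points.

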# ASSESSMENT OF EFFICACY

The primary endpoint in the efficacy trial is RFS after 12 months. Data from the one-year postoperative clinical follow-up that is registered in the HIPEC registry will be retrieved. Besides the site of relapse, also the date of recurrence is retrieved. It is defined as the date of the radiological examination that identifies the recurrence. Crude overall survival will also be assessed at the end of the trial follow-up as a secondary endpoint for the trial. The HIPEC registry is automatically connected with the Swedish death registry and therefore the overall survival follow-up is completely automatic as to the date of death. However, cause of death will also be retrieved from the cause of death registry in order to perform exploratory analyses of cancer specific survival. Likewise, quality-of-life will be retrieved from the HIPEC registry as well.

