## Clinical and laboratory assessments

### Timing and method of the assessment

The dose titration is assessed continuously as each dose level is completed. All morbidity data is retrieved from the HIPEC registry.

Patient follow-up:

Mandatory

- Abdominal and thoracic CT scan at baseline before surgery and 12 months postoperatively.
- Treatment administered (CRS+HIPEC+EPIC variables)
- Morbidity to be submitted within 30 days from treatment administration. SAE and SUSAR are to be reported immediately (a separate section will make this possible in the HIPEC registry)
- Overall survival follow-up at
- 5 years from the HIPEC registry

Clinical routine

- The following follow-up is standard in Sweden after CRS+HIPEC: CT scan and tumor markers every 6 months for 2 years and then annually for another 3 years. Since all these follow-ups are not included in the HIPEC registry, we will not include them in the schedule of investigational events.
- EORTC QLQ-C30, CR29, and STO22 questionnaires filled out at baseline, 3, 12 and 36 months after surgery using the established QoL database. All patients are included in the quality-of-life registry as part of the clinical quality assurance follow-up, unless they specifically have requested not to be included.

Optional: Sending intraoperative tumor tissue to Uppsala for chemoresistance testing within 48 hours. Tissue is discarded right after testing. No biobanking will occur.

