## Follow-up of adverse events and serious adverse events

All patients are followed up within 3 months postoperatively within normal clinical routine to evaluate the potential long-term effects of previous adverse events. If an AE is not recovered after 3 months, it will be followed up until recovered or stabilized.

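### Section 9.3 has a single level of withdrawal that ends all follow-up, so recurrence and survival outcomes that could still be retrieved from registries go missing avoidably

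*Protocol*

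**What the plan says.** Section 9.3 describes one form of withdrawal: "Naturally, patients may opt to withdraw for any reason from the trial". Data already obtained are kept ("all data collected up to the point of withdrawal will be included in the trial"). After that: "No further quality of life questionnaires will be sent out after withdrawal has been requested. All other follow-up will also be discontinued". No exception is made for registry data, and nothing elsewhere in the protocol restores one.

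Other sections describe how the outcomes arise:
- Section 11, on death: "The HIPEC registry is automatically connected with the Swedish death registry and therefore the overall survival follow-up is completely automatic".
- Section 8.1: recurrence, quality-of-life and morbidity data can be retrieved automatically from the registry. Section 8.3 schedules RFS and overall survival as HIPEC registry items.
- Section 11.1.1: a CT at 12 months is mandatory, and six-monthly CT for two years is routine care, but not all routine follow-ups enter the registry. On quality of life: "All patients are included in the quality-of-life registry as part of the clinical quality assurance follow-up", unless they have asked not to be.
- Section 13.7, on intention-to-treat: "Thus, all patients being randomized are included in the trial".
- Section 12.7, on adverse events: "If an AE is not recovered after 3 months, it will be followed up until recovered or stabilized". No exception is made for withdrawn patients.
- Section 10.5: treatment is not blinded, but the radiologists are not told the allocation.
- Section 13.6: multiple imputation is optional for data that cannot be obtained.

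**The concern.** Treatment is a single perioperative episode. Sections 9.3 and 9.4 themselves say that it follows randomization within hours and that withdrawal in between should in principle not occur. Nearly every withdrawal will therefore come from a patient who has had the full allocated treatment, and what it ends is data collection.

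Part of that collection asks nothing more of the patient. Date of death needs no contact at all. A recurrence already recorded in the registry needs only to be read out. Stopping both by default discards outcomes that the intention-to-treat comparison needs.

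Allocation is known, and arm B adds irinotecan and intraperitoneal 5-FU, so the decision to withdraw can depend on arm and on how the patient is doing. Blinded CT reading does not help when the result is never retrieved. Imputation would rest on an assumption about the withdrawn patients that the trial's own data cannot test. A separate analysis plan cannot repair this, because the protocol itself stops the collection.

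**Working it through.** **1. The plan's own sample size.** Inputs from section 13.3: 12-month RFS 50% vs 66%, alpha 5% (taken as two-sided), the stated beta of 80% read as power, 148 per arm, 10% allowance, 163 per arm.
- Pooled two-proportion formula: n = [1.96·√(2·0.58·0.42) + 0.842·√(0.50·0.50 + 0.66·0.34)]² / 0.16², which rounds up to 149. The arcsine version gives 147.95, i.e. 148. The stated figure is reproduced.
- Allowance: 148 × 1.10 = 162.8, i.e. 163. Dividing instead, 148/0.90 gives 165. The difference is not material here.

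**2. Power.** With 163 per arm and nothing missing, power is 83.6%. With 5% missing (154.8 per arm) it is 81.7%, and with 10% missing (146.7 per arm) 79.6%. Within the allowance power stays near 80%, so loss of power is not the issue.

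**3. Bias when there is no true effect.** The protocol gives no withdrawal rate, so I assume a range of 2% to 10%. Assume also that true RFS is 50% in both arms, that a fraction m is missing in one arm only, that a proportion r of those would have recurred, and that complete cases are analysed. The observed RFS in that arm is [0.50 − m(1 − r)]/(1 − m). The type I error uses a normal approximation with 163 patients in one arm and 163(1 − m) in the other.

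| m | r | Observed RFS | Bias (points) | Two-sided type I error |
|---|---|---|---|---|
| 2% | 100% | 0.500/0.98 = 51.0% | +1.0 | 5.4% |
| 5% | 100% | 0.500/0.95 = 52.6% | +2.6 | 7.6% |
| 10% | 100% | 0.500/0.90 = 55.6% | +5.6 | 16.5% |
| 2% | 75% | 0.495/0.98 = 50.5% | +0.5 | 5.1% |
| 5% | 75% | 0.4875/0.95 = 51.3% | +1.3 | 5.6% |
| 10% | 75% | 0.475/0.90 = 52.8% | +2.8 | 7.8% |

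**4. Worst-to-best-case range.** Suppose 50% vs 66% is observed and a fraction m is missing in each arm. The difference then lies between 0.16(1 − m) − m and 0.16(1 − m) + m:
- m = 2%: 13.7 to 17.7 points
- m = 5%: 10.2 to 20.2 points
- m = 10%: 4.4 to 24.4 points

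**5. Sections 9.3 and 12.7 side by side.** Section 9.3 stops all follow-up with no exception for adverse events. Section 12.7 follows an unresolved event to recovery or stabilization with no exception for withdrawal. For a withdrawn patient with an open event, the text does not say which governs.

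**The case against.** Several points on the other side stand and limit the claim.

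- **Intention-to-treat.** A reader might infer that section 9.3 contradicts section 13.7. It does not. Withdrawn patients stay in the analysis set with their data up to withdrawal. The result is incomplete outcomes within that set.
- **Who counts as withdrawn.** A reader might infer that a patient who merely declines telephone calls loses all outcome data. The text does not say so, because section 9.3 concerns patients who leave the trial. The fair criticism is that it offers them no intermediate option. Section 16.4 makes collection and processing of data part of consent, so stopping collection is a recognisable, cautious choice, and an explicit refusal of further data use must be honoured.
- **Patient involvement.** A reader might infer that recurrence, like death, is captured without the patient. That holds in full only for date of death. The 12-month CT must be attended and its reading registered, and not all routine CTs reach the registry. How much RFS information could be recovered is therefore uncertain.
- **Interim safety review.** A reader might infer that the rule undermines this review. It rests largely on complications in hospital or within 30 days, and on mortality. Only information on late sequelae is exposed.
- **Adverse events.** Section 12.7 places the three-month follow-up within normal clinical routine, which leaving a trial does not end. The two sections still do not refer to each other.
- **Size.** The withdrawal rates are assumed, and the 10% allowance also covers protocol violations. The direction is assumed too: sections 16.2 and 16.3 report neutropenia as a favourable prognostic factor, so toxicity-related withdrawal need not remove patients with a poor outlook. The main RFS analyses in section 13.2.1 are struck through in favour of an appendix not available here. In a time-to-event analysis, withdrawn patients contribute until censoring. The figures above cannot be tied to the current primary analysis.

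**Conclusion.** The point holds in a limited form. Section 9.3 has one withdrawal rule that ends all follow-up, although vital status, and recurrence already in the registry, could still be retrieved. This makes some 12-month RFS and overall survival data missing avoidably, possibly in relation to arm and outcome, in an unblinded trial. It weakens the intention-to-treat analysis without contradicting it.

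The size cannot be established from the protocol. Under the one-sided, all-recurred assumption the bias runs from about 1 point at 2% missing to 5.6 points at 10%, against a design difference of 16 points. With a single perioperative treatment, withdrawal may well be rare, and at 2% the effect is small. These figures are illustrations that assume a complete-case comparison of proportions.

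**What to change.** Replace the last sentence of section 9.3 with two levels of withdrawal:

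- (a) Withdrawal from trial contacts and questionnaires. Retrieval of registry recurrence, of routine CT results recorded in the registry, and of vital status continues.
- (b) Explicit objection to further data use. Collection stops.

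Record the type, date and reason of each withdrawal, by arm, and put matching wording in the patient information. Reconcile sections 9.3 and 12.7 so that both state whether unresolved adverse events are followed after withdrawal.

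The cost is a protocol amendment, with no new visits and no change to the 326 patients. Patients already enrolled under the present wording may need updated information or renewed consent before later registry data are used. The automatic death link is described for Sweden only, so the pending Danish and Norwegian sites would need their own source of vital status. The gain is mainly protection against bias; little power is recovered.
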